### Methods in Analysis to Handle Protocol Non-Adherence and Any Statistical Methods to Handle Missing Data

The study will be analyzed according to the intention to treat principle. Patients who are hospitalized, transplanted or who die prior to receiving a MedRec will be excluded from the final analysis. Missing data will not be imputed.

### Plans to Give Access to the Full Protocol, Participant-Level Data, and Statistical Code (31c)

The full protocol will be published online, and the anonymous participant-level data required to replicate the final study manuscript will be made available within 3 months of publication.

### Oversight and Monitoring

#### Composition of the data monitoring committee, its role, and reporting structure (5d and 21a)

Not applicable.

### Adverse Event Reporting and Harms

MedSafer reports have been extensively tested on older adults with polypharmacy in the acute care setting (including patients receiving maintenance hemodialysis).^
16
^ If a clinician suspects that a report contains an erroneous recommendation or that an adverse event has occurred secondary to the intervention, they will contact the study team to report it.

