^ MedSafer stratifies deprescribing opportunities into high-risk, intermediate-risk, or little added value categories. High risk implies there is an elevated risk of developing ADEs; intermediate risk implies that the harms must be weighed against the benefits of the drug; and drugs of little added value simply increase the pill burden of a patient or have evidence demonstrating no effect. Examples of a typical deprescribing report and of different drugs that fall into the 3 categories can be found in the Supplement of the MedSafer Study.^
16
^ Our large cluster randomized clinical trial of older adults hospitalized in the acute care setting (N = 5698) included 140 patients receiving maintenance hemodialysis. The net deprescribing rate among dialysis patients was 9.4% (95% confidence interval [CI] = 1.3%-17.6%) higher in the intervention period compared with the control period. While effective, the general population in the study benefited from a much higher rate of deprescribing (absolute increase of 22.2%, 95% CI = 16.9%-27.4%).^
16
^ At that time, no dialysis-specific rules were integrated into the MedSafer software, and patients were enrolled during a time of acute illness.

Since then, McIntyre et al^
15
^ have developed deprescribing algorithms specifically for hemodialysis patients in a quality improvement study.^4,8^ However, like most guidelines, there are barriers to implementation and uptake. Guidelines for deprescribing contain long lists of rules that preclude memorization; some may contain conflicting recommendations for patients taking 10 to 15 medications; and not all guidelines explain how to deprescribe (eg, when and how to taper and what rebound symptoms to watch out for).^
2
^,^21-23^ We therefore integrated the dialysis-specific deprescribing recommendations into the MedSafer ruleset, coupled them with links to patient deprescribing empowerment brochures, and added instructions for tapering where required.

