## Discussion

This quality improvement study integrates electronic deprescribing decision support with the usual process of MedRec taking place on our dialysis units. To our knowledge, this is the first study to test the implementation of the new dialysis-specific deprescribing algorithms in a real-world setting. Potential implications of this quality improvement study include reducing the number of PIMs prescribed and decreasing pill burden by reducing the mean number of medications prescribed. This is a pragmatic study as it is built into the existing workflow for performing MedRec at our hospital center. As many dialysis units have similar MedRec procedures, we expect our findings would be scalable to other centers.

There are barriers to deprescribing during routine MedRec in hemodialysis. In fact, clinicians can lack sufficient time to complete a medication review and subsequently deprescribe; patient values and previous lived experiences with their medications, their perceived therapeutic effects, and potential adverse events are important factors to consider.^
37
^ Because of their chronic renal disease and complex medication regimens, patients on dialysis can also experience cognitive impairment that may affect the clinician’s ability to comprehensively perform medication reconciliation given already limited time constraints.^
21
^ Patients may also lack sufficient resources to learn about the medications they are taking, including their potential harms. The therapeutic relationship between the patient and the clinician can also influence initiation of a deprescribing trial or affect readiness to attempt a drug deprescription.^38,39^ This study aims to overcome these barriers through its methodology; we aim to address the lack of time by providing nephrologists with prepared deprescribing reports.

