Whenever possible, patients should be involved in the deprescribing process. Patients may be reluctant to have certain drugs deprescribed because they have been taking them for a long time, and/or are wary of withdrawal or rebound side effects, such as acid reflux, inability or difficulty sleeping, or pain. This is a potential challenge that we hope our study methodology addresses by providing patients with deprescribing empowerment brochures for some relevant drug classes. The goal of the deprescribing brochures is to generate cognitive dissonance with an introductory quiz and increase motivation to deprescribe. We also aim to overcome the challenge of limited patient resources by providing patients with deprescribing brochures that use accessible language.

This study has several important limitations that need to be recognized. First, the study cohort is closed, so the sample size may, over the course of the study, decrease due to deaths, hospitalization, or transplant. We do not expect this to majorly affect the overall sample size as the duration of the intervention is short (taking place over 2 months). In this study, we do not currently have the resources to follow patients long term and are investigating the short-term impact of providing deprescribing reports on a single MedRec. The long-term impact on polypharmacy would need to be the subject of a further funded study. This study is also not powered to observe an effect on hard outcomes such as death, adverse drug events or hospitalization, especially in the short term. We will be reporting the number of gastrointestinal bleeds numerically, but we will not be powered to demonstrate a difference between intervention groups.^
40

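### Apart from gastrointestinal bleeds, post-MedRec harms are recorded only when a clinician suspects the intervention, so they cannot be compared between units; the testing cited alongside predates the dialysis-specific rules

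*Protocol article*

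**What the plan says.** All references are to the protocol article.

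- **Adverse Event Reporting and Harms.** The section opens with earlier experience: "MedSafer reports have been extensively tested on older adults with polypharmacy in the acute care setting (including patients receiving maintenance hemodialysis"). It then sets one reporting route. A clinician who suspects an erroneous recommendation, or "that an adverse event has occurred secondary to the intervention, they will contact the study team to report it".
- **Intervention description; Who Will Be Blinded?** The control unit performs its usual MedRec at the same time, without reports or brochures.
- **Outcomes; Discussion.** Gastrointestinal bleeds will be counted overall and for each unit, with no attribution condition. The Discussion says the study lacks the power to compare them.
- **Recruitment.** Patients who die, are transplanted, or are hospitalized and so miss the MedRec will be described and left out of the analysis.
- **Plans for Assessment and Collection of Outcomes; Data Management.** The post-MedRec data named for both units are medication changes taken from NephroCare, with comorbidity data updated in MedSafer.
- **Background and Rationale.** The earlier acute-care trial (N = 5698) "included 140 patients receiving maintenance hemodialysis". Of that trial the article says: "At that time, no dialysis-specific rules were integrated into the MedSafer software, and patients were enrolled during a time of acute illness". The rules came later: "We therefore integrated the dialysis-specific deprescribing recommendations into the MedSafer ruleset".
- **Discussion.** The authors write that, to their knowledge, "this is the first study to test the implementation of the new dialysis-specific deprescribing algorithms in a real-world setting". They also note that patients may be reluctant because they "are wary of withdrawal or rebound side effects, such as acid reflux, inability or difficulty sleeping, or pain".

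**The concern.** The general rule needs two things before an event is recorded: the event, and a clinician's suspicion that the intervention caused it. The second condition can be met on only one unit. Control patients also have drugs stopped or tapered during MedRec, and any harm that follows is outside the rule because no intervention was delivered to blame. On the intervention unit, the rule yields what a clinician who knows the allocation attributes to MedSafer.

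The study hopes to show more deprescribing. A natural companion question is whether more harm came with it. Bleeds aside, a count that is filtered by attribution on one unit and empty by rule on the other cannot answer that, even as a plain table. The harms section also sets the earlier testing beside this light procedure. A reader who sees few or no reports could take the two together as support for a ruleset that was not in that testing.

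**Working it through.** **1. The plan's own design figure.** The article gives no figure for adverse events. Its one computed figure is the detectable difference: 10% versus 25%, N = 214, 80% power, two-sided alpha 0.05, about 1:2 allocation. I used the pooled-variance normal approximation without continuity correction, with r = 2 and pooled proportion (0.25 + 2 × 0.10)/3 = 0.15:

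n₁ = [1.960 × √(0.15 × 0.85 × 1.5) + 0.842 × √(0.25 × 0.75 + 0.10 × 0.90/2)]² / 0.15² ≈ 71

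The total is 71 + 142 = 213, against 214 stated. The figure reproduces. The present point does not depend on it, but it supplies the denominators below.

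**2. Who falls under the rule.**

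| | Intervention | Control |
|---|---|---|
| Patients | 85 | 153 |
| With a PIM (90% assumed in the plan) | 76.5 | 137.7 |
| Deprescribing rate in the design | 25% | 10% |
| Patients expected to have a PIM deprescribed | 0.25 × 76.5 ≈ 19 | 0.10 × 137.7 ≈ 14 |
| Can the general rule be triggered? | Yes, on suspicion | No |

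Under the design assumptions, about 14 of 33 patients with a PIM deprescribed (42%) are on the unit where the rule cannot operate. The control zero is therefore not trivial: deprescribing is expected there too.

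**3. Illustration with assumed event rates.** The article gives none, so these only show the form of the distortion. Suppose the true rate of some harm is the same on both units.

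| Assumed true rate | Expected events, 76 intervention patients | Expected events, 138 control patients | Control events recorded by the rule |
|---|---|---|---|
| 2% | 1.5 | 2.8 | 0 |
| 5% | 3.8 | 6.9 | 0 |
| 10% | 7.6 | 13.8 | 0 |

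The number recorded on the intervention unit depends on how often clinicians suspect MedSafer, which cannot be estimated from the article.

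**4. What lies outside the rule.** Bleeds are to be reported for each unit, so they are not subject to the attribution filter. Deaths and hospitalizations that prevent a MedRec are described, but they precede the MedRec and cannot reflect deprescribing at it. For other harms after the MedRec, the article names no capture on both units.

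**5. The earlier testing.** Dialysis patients were 140/5698 = 2.5% of that trial. By the Background's account, none was managed with dialysis-specific rules, and all were enrolled during acute illness. The present patients are outpatients and the rules are new to the software. The article reports no adverse-event result from the earlier trial, so no bound on risk can be carried over from it.

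**The case against.** The other side has real force on several points.

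- **A harm is counted on both units.** A reader might infer that the study can report only one-sided harms. The documents do not support that: the bleed count is planned for each unit without attribution. The article does not say how bleeds are found, but that detail may sit in the full protocol and is not held against it here.
- **The route is a safety signal, not an outcome.** An intervention-attributed count of zero on a unit without the intervention is correct by definition, and no between-unit comparison of it is planned. This stands. It means the rule is not a biased estimator. It does not supply the missing comparison, and no other described route does.
- **The limits are disclosed.** The Discussion says the study is short, covers a single MedRec and is not powered for adverse drug events. That answers a complaint about precision. Unequal ascertainment is a different matter, which no sample size repairs.
- **The sentence on earlier testing is literally true.** A reader might infer that it is false, or that the reporting procedure expressly rests on it. Neither is supported. The testing did include hemodialysis patients, the Background openly states that the dialysis rules were absent, and the link to the procedure is inferred from the two statements sharing a short section. MedSafer has also been studied in long-term care, the dialysis algorithms came from a hemodialysis quality improvement study, and the authors' claim to be first concerns implementation. What remains is that the harms section omits a caveat made elsewhere.
- **Symptoms may not be charted evenly.** Nothing shows that NephroCare records reflux, sleep difficulty or pain, and clinicians aware of the intervention may note them more readily. This stands and narrows the remedy.

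**Conclusion.** The point holds in limited form. Apart from gastrointestinal bleeds, the article's only described route for harms after MedRec requires suspicion of the intervention, so it returns zero for the 153 control patients whatever their true event rate. Those harms cannot be set side by side, even descriptively. The earlier testing cited in the same section did not include the dialysis-specific rules.

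This does not affect the primary analysis, and the article makes no comparative safety claim. It is an inexpensive improvement worth making, not a fatal flaw.

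The conclusion assumes that the harms section is the complete account of general adverse-event capture; a fuller protocol with attribution-free capture on both units would remove the first part. The figure of 14 control patients with a PIM deprescribed rests on the plan's own 90% and 10%. The event rates of 2% to 10% are illustrative only.

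**What to change.** 1. In Adverse Event Reporting and Harms, keep the spontaneous route for suspected report errors and for events suspected to be caused by the intervention.
2. In the chart review that supplies post-MedRec medication changes for both units, and together with the planned bleed count, also record death, hospitalization, and falls or fractures. Record them regardless of suspected cause, over the same window per patient counted from the MedRec, with its length fixed before extraction starts.
3. If withdrawal or rebound symptoms are collected, label them exploratory and state that clinicians who know the allocation may chart them unevenly.
4. Tabulate counts and denominators by unit, descriptively, with no powered comparison.
5. Qualify the statement "MedSafer reports have been extensively tested on older adults with polypharmacy in the acute care setting" by adding that the dialysis-specific rules were not part of that testing.

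**Cost.** A few more fields for 238 patients, some abstraction time, and extraction that waits until the last patient's window closes. Charted events will be under-recorded, and a common source reduces unequal ascertainment between units without guaranteeing its absence. The wording change costs one sentence. Nothing in patient care changes.

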### Frequency and Plans for Auditing Trial Conduct

Not applicable.

### Plans for Communicating Important Protocol Amendments to Relevant Parties (eg, Trial Participants, Ethical Committees)

Not applicable.

### Dissemination Plans

Study results will be made available through publication in a peer-reviewed indexed journal. Study results will be shared at a leading annual conference on nephrology and/or general internal medicine.

## Discussion

This quality improvement study integrates electronic deprescribing decision support with the usual process of MedRec taking place on our dialysis units. To our knowledge, this is the first study to test the implementation of the new dialysis-specific deprescribing algorithms in a real-world setting. Potential implications of this quality improvement study include reducing the number of PIMs prescribed and decreasing pill burden by reducing the mean number of medications prescribed. This is a pragmatic study as it is built into the existing workflow for performing MedRec at our hospital center. As many dialysis units have similar MedRec procedures, we expect our findings would be scalable to other centers.

There are barriers to deprescribing during routine MedRec in hemodialysis. In fact, clinicians can lack sufficient time to complete a medication review and subsequently deprescribe; patient values and previous lived experiences with their medications, their perceived therapeutic effects, and potential adverse events are important factors to consider.^
37
^ Because of their chronic renal disease and complex medication regimens, patients on dialysis can also experience cognitive impairment that may affect the clinician’s ability to comprehensively perform medication reconciliation given already limited time constraints.^
21
^ Patients may also lack sufficient resources to learn about the medications they are taking, including their potential harms. The therapeutic relationship between the patient and the clinician can also influence initiation of a deprescribing trial or affect readiness to attempt a drug deprescription.^38,39^ This study aims to overcome these barriers through its methodology; we aim to address the lack of time by providing nephrologists with prepared deprescribing reports.

Whenever possible, patients should be involved in the deprescribing process. Patients may be reluctant to have certain drugs deprescribed because they have been taking them for a long time, and/or are wary of withdrawal or rebound side effects, such as acid reflux, inability or difficulty sleeping, or pain. This is a potential challenge that we hope our study methodology addresses by providing patients with deprescribing empowerment brochures for some relevant drug classes. The goal of the deprescribing brochures is to generate cognitive dissonance with an introductory quiz and increase motivation to deprescribe. We also aim to overcome the challenge of limited patient resources by providing patients with deprescribing brochures that use accessible language.

This study has several important limitations that need to be recognized. First, the study cohort is closed, so the sample size may, over the course of the study, decrease due to deaths, hospitalization, or transplant. We do not expect this to majorly affect the overall sample size as the duration of the intervention is short (taking place over 2 months). In this study, we do not currently have the resources to follow patients long term and are investigating the short-term impact of providing deprescribing reports on a single MedRec. The long-term impact on polypharmacy would need to be the subject of a further funded study. This study is also not powered to observe an effect on hard outcomes such as death, adverse drug events or hospitalization, especially in the short term. We will be reporting the number of gastrointestinal bleeds numerically, but we will not be powered to demonstrate a difference between intervention groups.^
40
^ This is a single-center study, and to influence outcomes such as these likely requires more than 6000 patients (based on our previous study of MedSafer in the acute care setting). This study is also not randomized; we aim to minimize (but cannot eliminate), through statistical adjustment, obvious baseline differences in comorbidities between the control and intervention units. Next, our study is not sufficiently powered to capture differences in rates of represcribing between the control and the intervention group. It should be noted that our study will capture prescribed/deprescribed drugs, and not *dispensed* drugs, or drugs actually taken by the patient. Another caveat is that our dialysis units do not have the support of a pharmacist, and so the MedRec process will be performed by the doctor and nurse on the unit. Finally, our study is taking place at an academic hospital center and so the patients may not resemble those treated in all dialysis centers. That said, the 2 units participating in the study tend to provide dialysis for general nephrology patients, and the intervention unit is attached to our community hospital site.

